### Inclusion criteria

· Patients over 18 years of age

· Informed consent

· De novo stenosis, re-stenosis (Peak Systolic Velocity (PSV) ratio > 2.5) or occlusion of the native SFA, all > 10 cm in length

· Popliteal artery is patent at the upper margin of the patella to the trifurcation

· Diameter of the native SFA and popliteal arteries are 5.0 to 7.5 mm

· Rutherford category 3-6

· Indication for surgical bypass

· Distal runoff at least 1 crural vessel without significant stenosis

· Resting ankle-brachial index (ABI) < 0.8 in the study limb prior to procedure

### Exclusion criteria

· Patient unsuitable for administration of contrast agent

· Pregnancy

· Dementia or altered mental status that would prohibit giving conscious informed consent

· Need for adjunctive major surgical or vascular procedures within 1 month

· Untreated flow-limiting aorto-iliac occlusive disease

· Unsuccessful ipsilateral percutaneous vascular procedure to treat inflow disease just prior to enrollment

· Previous ipsilateral bypass surgery or stent-placement

· Femoral or popliteal aneurysm of target vessel

· Non-atherosclerotic disease resulting in occlusion (e.g. embolism, Buerger's disease, vasculitis)

· Severe medical co morbidities (untreated coronary artery disease/congestive heart failure, severe chronic obstructive pulmonary disease, metastatic malignancies, dementia, etc.) or other medical condition that would preclude compliance with the study protocol

· Major distal amputation (above the trans metatarsal) in the study limb

· Any previously known coagulation disorder, including hypercoagulability

· Contraindication to anticoagulation or antiplatelet therapy

· Known allergies to stent or stent-graft components

· History of prior life-threatening reaction to contrast agent

· Patients with known hypersensitivity to heparin, including those patients who have had a previous incidence of heparin-induced thrombocytopenia (HIT) type II

· Planned surgical procedure or major amputation to occur after enrollment of the patient

### Recruitment

Patients with symptomatic peripheral arterial disease of the superficial femoral artery with a Rutherford category 3-6 [15] may be included in the study and will be recruited among the 5 participating centers.

### Randomization

Randomization will be performed during the out patient department visit in which the patient is included. The including physician will call the telephone number provided by the principle investigator. The person answering the phone will draw an envelope from a box of plain white envelopes containing the randomization choice. The envelopes are divided in batches of 20 and randomization is stratified by center.

### Imaging

Ultrasound imaging screens all patients included in the study. Additionally, computed tomography angiography (CTA) or magnetic resonance angiography (MRA) will be performed. These imaging studies will be performed according to the local protocol of the participating centers. The lesions in the SFA will be categorized according to the Trans Atlantic Intersociety Consensus (TASC)-II criteria. Type B, C, and D lesions may be included.

## Treatment details

### Endovascular technique

Antibiotic prophylaxis is administered. Preferably a percutaneous technique is used, but in case of a flush occlusion or a diseased common femoral artery, an open approach is allowed. The SFA may be approached in a contralateral retrograde or an ipsilateral antegrade fashion. When there is a concomitant lesion in the common or profunda femoral artery an endarterectomy may be performed followed by the endoluminal bypass. Heparin (5000 I.U.) is administered. The diseased segment of the SFA is passed, either endoluminal or sub-intimal and a re-entry is created distally. The segment is pre-dilated with a regular angioplasty balloon and the endografts are positioned from distal to proximal without or with minimal or no oversizing. The entire diseased segment is covered with the stentgrafts and the stentgrafts are post dilated with an angioplasty balloon with the same size as the stent graft. Control angiography is performed routinely and the access is closed using a closure device, according to local protocols.

The used stent graft is the heparin-bonded Viabahn Endoprothesis (W.L. Gore & associates, Flagstaff, AZ), which is a self-expanding helical nitinol stent covered with a heparin-bonded thin polytetrafluorethylene (ePTFE) tube. The size of the stentgraft should be at least 6 mm.

Post procedurally, all patients will be treated with acetylsalicylic acid 80 mg and clopidogrel 75 mg for the first year unless oral anticoagulation is indicated for other reasons. After 1 year patients may be switched to 1 thrombocyt aggregation inhibitor. All patients receive statin treatment, started before the intervention.

### Open surgical technique

The surgical femoropopliteal bypass is performed according to local protocols. Preferably the greater saphenous vein is used as conduit in all patients. The used vein has a diameter of at least 3.5 mm. Pre-operative vein mapping may be performed, but is not obligatory. When the great saphenous vein is unavailable or unsuitable a prosthetic graft may be used. When a prosthetic conduit is used the participating surgeon will explicit this choice. All patients will be included in the intention-to-treat analysis.

Post procedurally, all patients will be treated with acetylsalicylic acid 80 mg and clopidogrel 75 mg for the first year unless oral anticoagulation is indicated for other reasons. After 1 year patients may be switched to one thrombocyt aggregation inhibitor. All patients receive statin treatment, started before the intervention.

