## Methods and design

### Study design

The design of the study is a multicentre prospective randomized controlled trial comparing the patency of the heparin-bonded endograft to the venous surgical bypass. Endpoints are primary patency after 1, 2 and 5 years, complications and quality of life.

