## Discussion

The aim of the present randomized trial is two-fold. First, it aims to compare patency rates of the endoluminal bypass, combined with the heparin-bonded technology, with the current gold standard, the venous femoro-popliteal bypass, the current gold standard. Second, it aims to demonstrate that an endovascular approach is associated with fewer complications and thus an improved quality of life. In order to have sufficient power, the trial was designed using a non-inferiority principle.

Data analysis will be performed in both an intention-to-treat as a per-protocol manner. The first will be performed to compare the endoluminal bypass with common surgical practice, namely that some patients will not have a vein usable for the bypass and that some endoluminal procedures will be converted to open surgery. The per-protocol analysis will give information about the performance of the endoluminal bypass itself.

There are several differences between the SuperB trial and previously published randomized trials [9,16]. The SuperB trial is the first trial using a heparin-bonded endograft and the inclusion criteria are chosen much broader since hybrid procedures, such as a reconstruction of the common femoral artery, are allowed. Moreover, the anti-platelet regime and the use of statins are standardized. The wide inclusion criteria are chosen because they mimic common surgical practice and thereby they reduce the risk on inclusion problems as was the case in the Scandinavian trial [16].

With the introduction of the heparin-bonded technology in the endograft the design of the stent has also been changed. The proximal edge of the endograft has no longer a straight, but a contoured edge (Figure 1). This adaptation will reduce infolding in case of oversizing, thereby maintaining laminar blood flow and preventing intimal hyperplasia and thus edges stenosis. The expected effect of the new endograft may therefore not only be attributed heparin-bonding technology.

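### The stated comparator is the venous bypass, but vein suitability need not be established before randomisation, so an analysis restricted to vein conduits would be selected in the surgical arm only

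*Protocol article*

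**What the plan says.** **Comparator.** The Study design section describes a trial "comparing the patency of the heparin-bonded endograft to the venous surgical bypass". The Study objectives and the Sample size calculation also name the venous bypass.

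**Control treatment as delivered.** Under Open surgical technique, vein is preferred, but "When the great saphenous vein is unavailable or unsuitable a prosthetic graft may be used". The abstract likewise describes the surgical arm as venous where possible.

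**Vein assessment.** The same section says "Pre-operative vein mapping may be performed, but is not obligatory" and "The used vein has a diameter of at least 3.5 mm". The diameter limit therefore applies to the vein that is used, not to entry. When a prosthesis is chosen, the surgeon makes that choice explicit.

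**Entry.** Neither the inclusion nor the exclusion list mentions the saphenous vein. The nearest item is "Indication for surgical bypass".

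**Randomisation.** "Randomization will be performed during the out patient department visit in which the patient is included". The only stratification factor is centre: "The envelopes are divided in batches of 20 and randomization is stratified by center".

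**Analysis sets.** Statistical analyses plans intention-to-treat and per-protocol analyses without defining the second. The Discussion justifies intention-to-treat as a reflection of everyday care and spells out what it means by this: "namely that some patients will not have a vein usable for the bypass and that some endoluminal procedures will be converted to open surgery". It gives the per-protocol analysis the purpose of showing how the endoluminal bypass itself performs.

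**The concern.** The article asks how the endograft compares with a venous bypass, and neither planned analysis clearly answers that.

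Intention-to-treat is a randomised contrast, but its control arm mixes vein and prosthetic conduits. A per-protocol analysis restricted to vein conduits would have the intended control. It would, however, remove patients without a usable vein from the surgical arm, where surgery reveals them, and leave their counterparts in the endograft arm, where nothing described in the article identifies them. The two groups would then differ by a patient characteristic as well as by treatment.

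If patients without a usable vein also do worse with an endograft, the contrast is biased against the endograft. If they do better, it is biased in its favour, and in a non-inferiority trial that is the direction that produces a false claim. An analysis plan written later can define the set, but it cannot create a pre-randomisation record that was never required.

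**Working it through.** **Inputs from the article.** Control patency at one year is 90%, the margin is 10 points, and there are 111 patients per group at alpha 5% and power 80% (Sample size calculation). Background one-year primary patency is 87% for venous and 74% for prosthetic bypass (Background).

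**Assumptions, because the article gives neither figure.** *s* is the share of patients without a usable vein. *g* is endograft patency in vein-suitable patients minus that in vein-unsuitable patients. No dropout is applied, and conversions to open surgery are ignored.

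**1. Reproduce the plan's figure.** With 90% in both arms and one-sided alpha 5%, n = 2 × 0.90 × 0.10 × (1.645 + 0.842)² / 0.10² = 111.3, in line with the stated 111. Power at 111 per arm is 79.9%. One-sided 2.5% would need 142, so the plan used one-sided 5%, and that level is used below.

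**2. Form of the bias.** Let pV be endograft patency in vein-suitable patients and cV vein-bypass patency.
- Endograft arm, not selected on vein: (1 − s) × pV + s × (pV − g) = pV − s × g.
- Surgical arm restricted to vein: cV.
- Observed difference: (pV − cV) − s × g. The bias is −s × g, and it is zero only if g = 0.

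**3. Size.**

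| s | g (points) | bias in absolute value (points) |
|---|---|---|
| any | 0 | 0 |
| 15% | 5 | 0.75 |
| 25% | 10 | 2.5 |
| 35% | 15 | 5.25 |

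A negative g reverses the sign.

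**4. Consequence at s = 25%.** 111 × 0.75 = 83 surgical patients remain. Power = Φ((0.10 − (pC − pT)) / SE − 1.645), where pC and pT are control and endograft patency and SE² = pC(1 − pC)/nC + pT(1 − pT)/nT.
- 83 vein versus 111 endograft, 90% in both (g = 0): SE 0.0435, power 74.3%.
- Same numbers, g = +10 points (endograft 87.5%): SE 0.0455, power 50.1%.
- Same numbers, g = −10 points (endograft 92.5%): SE 0.0413, power 91.6%.
- Both arms restricted by a perfect pre-randomisation record, 83 versus 83: SE 0.0466, power 69.2%, no bias.

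**5. False non-inferiority.** Suppose the endograft is truly 10 points worse in vein-suitable patients (80% versus 90%), so the nominal error is 5%. With g = −10 points the error is 10.9% at s = 20% and 15.0% at s = 30%. With g = +10 points it falls to 2.1% and 1.3%.

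**6. What intention-to-treat compares with.** On the article's own background rates, control patency is 87% × (1 − s) + 74% × s. At s = 10% this is 85.7% and at s = 40% it is 81.8%. Both are below the planned 90%, and neither is a venous-bypass rate.

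**The case against.** The strongest objection is that the criticised analysis is inferred. Nowhere does the article say that per protocol means vein conduit only. A surgical patient given a prosthesis because the vein was unsuitable has followed the protocol, and a conventional per-protocol set could keep that patient. The stated purpose of that analysis concerns the endoluminal bypass, not the vein. This stands, and it makes the point conditional. It does not remove it: if prosthetic recipients are kept, no planned analysis isolates the venous comparator.

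Three stronger readings are tempting but unsupported.
- *Vein status is not recorded before randomisation.* The case report forms and the full protocol are not shown, and mapping is permitted. The text shows only that assessment is not required.
- *Every endograft patient stays in the per-protocol set.* The Discussion passage that suggests dropping patients without a vein equally suggests dropping endoluminal cases converted to open surgery. The arm would be endograft patients regardless of vein suitability, minus conversions.
- *Nothing later could repair the comparison.* Earlier vein harvest and vein diameter might still be ascertained in endograft patients after allocation, and duplex is done at each visit. A record made before allocation is cleaner, but it is not the only route.

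It is also fair that the design choice is explained. The broad entry criteria are meant to mirror practice and ease recruitment, and intention-to-treat remains randomised. Departing from randomisation is a general limitation of per-protocol analyses. What is particular here is that the exclusion would depend on a patient characteristic visible in only one arm.

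Finally, the share, the gap and its direction are all assumed. The fall in power from 74% to 50% is one illustration, not a prediction.

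**Conclusion.** The point holds in conditional form. The article names the venous bypass as comparator but does not make vein suitability an entry criterion or a stratification factor, and does not require it to be assessed before randomisation. Intention-to-treat is sound as a randomised comparison with vein-or-prosthetic surgery. Any analysis that drops prosthetic recipients from the surgical arm alone is not protected by randomisation.

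The bias equals s × g: about 0 to 5 points in either direction for assumed shares of 15-35% and gaps of 0-15 points, against a 10-point margin. A reader might infer that the per-protocol result must be biased against the endograft. The article supports neither a direction nor a non-zero gap. The planned sample size is not in dispute; it reproduces.

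**What to change.** 1. Before the randomisation call, have the including physician record for every patient whether a usable vein is expected (yes or no). The answer would come from history and any ultrasound already done, with no extra imaging required.
2. Keep all patients in intention-to-treat, and describe that result as a comparison with vein-or-prosthetic surgery.
3. Define any comparison with venous bypass as the as-randomised comparison, in both arms, of patients recorded as vein-usable.
4. State whether prosthetic recipients belong to the per-protocol set. Label any analysis that removes them from the surgical arm alone as non-randomised and supportive.

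**Cost.** One field on the inclusion form and one analysis-set definition, with no change to treatment. The restricted comparison is smaller: if 25% lack a vein, 83 per arm and about 69% power, assuming perfect classification. Without mapping, classification will be imperfect. Some patients recorded as vein-usable will still receive a prosthesis, so the comparison is strictly with surgery in patients expected to have a usable vein.

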### Follow-up

Follow-up is planned at 1, 3, and 6 months. Afterwards patients will be seen each 6 months until 2 years. From 2 to 5 years patients will be evaluated annually. Duplex ultrasound imaging, ankle-brachial indices, and QOL scores will be measured at all above mentioned time points. All primary and secondary endpoint are registered as defined in the study protocol.

### QOL scores

• RAND-36 is a multidimensional measurement of health. This will also be used in both groups

• WIQ (Walking Impairment Questionnaire) is especially designed for patients with claudication, and will only be used in patients treated for claudication.

These scores are taken prior to the intervention and at defined times afterwards (i.e. 1 day, 1 week, 1 month, etc).

### Data collection

Data will be collected at the recruitment centre by means of case report forms (CRF's). The copies of the CRF forms will be sent to the coordinating center (Rijnstate Hospital) where all data will be entered in the central database and controlled by an independent monitor. The participating centers will be informed about the current status of recruitment and adverse events via a newsletter every 3 months. Additionally, there will be regular contact between the principle investigator and the contact persons from the participating centers.

### Statistical analyses

Data concerning the 1, 2, and 5 year follow-up will be analyzed for both study groups on an intention-to-treat and a per-protocol manner by student t-test (normal distribution) of Mann Whitney U-test (skewed distribution). Corrections will be made for study centre. Additionally, in case of sufficient numbers, the data will be analyzed for different TASC II categories; otherwise the analyses will be additionally adjusted for TASC II categories. Patency rates will be presented as Kaplan Meier curves including censoring.

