### Study objectives

The aim of the study is to demonstrate that the heparin-bonded endograft provides equal patency rates compared to the venous surgical femoro-popliteal bypass. In addition we hypothesize that patients receiving a heparin-bonded endograft show better quality of life at 30-days compared to patients who were surgically treated.

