### Sample size calculation

The assumption has been made that the heparin-bonded endoluminal bypass will have a similar cumulative primary patency at one year compared to the venous bypass. For a non-inferiority trial with an effect size of 90% and a margin of 10%, 111 patients per group are needed (alpha 5%, power 80%). The effect size of 90% refers to an estimated patency rate at one year in the surgical control arm.

The assumption has been made that the heparin-bonded endoluminal bypass will have an increase in QOL, as measured by a 10-point increase in the SF-36 score, at 30 days follow-up. With a standard deviation of 20, 63 patients per group are needed (alpha 5%, power 80%).

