### Primary endpoints

The primary endpoints of the study are the primary patency at 1-year follow-up. In addition the quality of life, using the RAND SF36 Questionnaire will be evaluated as a primary endpoint.

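### The quality-of-life hypothesis is set and powered at 30 days, but the analysis section names only 1, 2 and 5 years, with tests that cannot carry its own adjustments

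*Protocol article*

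**What the plan says.** Five sections of the protocol article bear on this point.

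- **Primary endpoints** gives quality of life primary status but no time point: "In addition the quality of life, using the RAND SF36 Questionnaire will be evaluated as a primary endpoint".
- **Study objectives** supplies the time point; the hypothesis is that "patients receiving a heparin-bonded endograft show better quality of life at 30-days compared to patients who were surgically treated".
- **Sample size calculation** powers the same contrast, "as measured by a 10-point increase in the SF-36 score, at 30 days follow-up", with SD 20, alpha 5% and power 80%, giving 63 per group. The trial itself is sized at 111 per group, from the patency comparison.
- **Follow-up** and **QOL scores** show that the data will exist. "Follow-up is planned at 1, 3, and 6 months", with quality of life measured at each visit, and "These scores are taken prior to the intervention and at defined times afterwards (i.e. 1 day, 1 week, 1 month, etc".
- **Statistical analyses** states "Data concerning the 1, 2, and 5 year follow-up will be analyzed for both study groups", by intention to treat and per protocol, using a t-test or, for skewed data, a Mann-Whitney U test. It adds a correction for study centre. It also plans separate analyses by TASC II category if numbers allow, and otherwise adjustment for that category. It mentions neither 30 days nor the baseline quality-of-life score.

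**The concern.** A primary endpoint needs one designated contrast. Someone working from the objectives and the sample size would test RAND-36 at 30 days. Someone working from the endpoint list and the analysis section could just as well test it at 1 year. These are different questions. The Background bases the expected benefit on less pain, earlier recovery and fewer early complications, and such an advantage may well have faded by 1 year. Quality of life is measured at many visits, so an undesignated time point leaves room to choose after the data are seen.

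The second problem is that the stated method does not fit the stated adjustment. A two-sample t-test or Mann-Whitney U test takes no covariates, so correction for centre or TASC II category requires a model or a stratified test, and none is named.

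Third, the patients range from Rutherford 3 to 6 and randomisation is stratified by centre only, so the design does not control chance imbalance in baseline quality of life. A baseline score is collected, but no use of it is stated.

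**Working it through.** **1. Time points side by side.**

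| Section | Quality-of-life time point |
|---|---|
| Primary endpoints | none given |
| Study objectives | 30 days |
| Sample size calculation | 30 days |
| Follow-up; QOL scores | baseline, 1 day, 1 week, 1 month and later |
| Statistical analyses | 1, 2 and 5 years |

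The 30-day contrast is hypothesised, powered and measured, but it does not appear among the stated analyses.

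**2. The plan's own figure.** Inputs from Sample size calculation: difference 10, SD 20, alpha 5%, power 80%. Sidedness is not stated.

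- Formula: n per group = 2 × (z_alpha + z_power)² × SD² / difference².
- Two-sided: 2 × (1.960 + 0.842)² × 400 / 100 = 62.8, so 63. This reproduces the stated number.
- One-sided: 2 × (1.645 + 0.842)² × 400 / 100 = 49.5, so 50. The plan evidently used a two-sided 5% test.
- The t-distribution version gives 64, with 79.5% power at 63, an immaterial difference.

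**3. Power at the planned size, without baseline adjustment.** With 111 per arm the standard error is 20 × √(2/111) = 2.68. Then 10/2.68 = 3.73, and 3.73 − 1.96 = 1.77, which gives about 96% power.

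**4. What baseline adjustment would add.** The documents give no correlation r between baseline and 30-day scores, so 0.3 to 0.7 is an assumed range. If SD 20 is the SD of a single score, ANCOVA multiplies the variance by 1 − r². The required n is 62.8 × (1 − r²), and the difference detectable with 80% power at 111 per arm is 2.80 × 20 × √(1 − r²) × √(2/111).

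| Assumed r | Variance factor | n per arm | Detectable difference at 111 per arm |
|---|---|---|---|
| no adjustment | 1.00 | 63 | 7.5 points |
| 0.3 | 0.91 | 58 | 7.2 points |
| 0.5 | 0.75 | 48 | 6.5 points |
| 0.7 | 0.51 | 33 | 5.4 points |

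**5. If SD 20 is instead the SD of a change score.** The plan's wording about an increase allows this reading. The single-score variance is then 400 / [2(1 − r)], and the ANCOVA residual variance is 400 × (1 − r²) / [2(1 − r)] = 400 × (1 + r)/2. Against a change-score t-test needing 63, ANCOVA needs 62.8 × 0.65 = 40.8 (41), 62.8 × 0.75 = 47.1 (48) and 62.8 × 0.85 = 53.4 (54) per arm at r = 0.3, 0.5 and 0.7. The gain remains but follows a different pattern, so the table in step 4 depends on its SD assumption.

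**The case against.** The other side has four fair arguments.

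- **The years may be data cuts.** The Publication of data section lists the same 1, 2 and 5 years as reporting points, and the analysis sentence does not say that nothing else is analysed. A 1-year data cut would contain the 30-day visit. A reader might infer that the plan moves the quality-of-life test to 1 year; the documents do not say so. It still stands that, even on this reading, the analysis section never designates the 30-day comparison.
- **Adjustment is promised.** A reader might infer from the named tests that the analysis is unadjusted. That is wrong, since corrections for centre and, conditionally, TASC II category are stated. The fault is that the named tests cannot deliver them.
- **Silence on baseline is not a decision to discard it.** The planned 10-point increase could mean a change score, and a t-test can be run on change scores. A statistical analysis plan that is not shown may settle this. On its own, this silence would not be a finding. It matters here because the stated method has to be replaced anyway, and the baseline score belongs in the replacement.
- **The efficiency figures do not measure the time-point mismatch, and they rest on an assumed correlation.** This is accepted. They show what the better model gains, not the cost of the inconsistency, which cannot be put as a number from the documents.

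**Conclusion.** The concern holds in a limited form. The 30-day quality-of-life contrast, primary and powered, is not among the stated analyses, and the sections conflict until reconciled. The t-test and Mann-Whitney U test cannot carry the promised corrections for centre and TASC II category. No use of the baseline RAND-36 is stated.

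The consequence is an undesignated primary contrast and avoidable imprecision. A reader might infer an underpowered comparison, but the arithmetic does not support that: unadjusted power at 111 per arm is about 96% for 10 points, assuming SD 20 and complete 30-day data in both arms. Adjustment would lower the required number from 63 to 58, 48 or 33 per arm at r of 0.3, 0.5 or 0.7, if SD 20 is a single-score SD. Both that reading and the correlations are assumptions. The point should be corrected before analysis, but it does not undermine the design.

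**What to change.** Add to the Statistical analyses section a statement to this effect: the primary quality-of-life analysis compares RAND-36 at 30 days between arms by ANCOVA, with baseline score, study centre and TASC II category as covariates, at a two-sided 5% level; later visits are secondary. Rutherford class (3 versus 4 to 6) may be added as a covariate.

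The statement should also name the RAND-36 score or domain to which the 10-point difference refers, because the QOL scores section calls the instrument multidimensional. It should say whether SD 20 belongs to a single score or to a change.

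TASC II category should stay in the model, since the plan already foresees adjusting for it. The t-test and Mann-Whitney sentence should not be narrowed in a way that ties it to patency, which the same section presents by Kaplan-Meier curves with censoring.

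The change is to wording only. Baseline and 1-month scores are already scheduled, so no new data, visits or patients are needed.
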